## Abstract

**Introduction:**

Approximately 70% of patients with stroke experience impaired arm function, which is persistent and disabling for an estimated 40%. Loss of function reduces independence in daily activities and impacts on quality of life. Muscles in those who do not recover functional movement in the stroke affected arm are at risk of atrophy and contractures, which can be established as early as 6 weeks following stroke. Pain is also common. This study aims to evaluate the feasibility of a randomised controlled trial to test the efficacy and cost-effectiveness of delivering early intensive electrical stimulation (ES) to prevent post-stroke complications in the paretic upper limb.

**Methods and analysis:**

This is a feasibility randomised controlled trial (n=40) with embedded qualitative studies (patient/carer interviews and therapist focus groups) and feasibility economic evaluation. Patients will be recruited from the Stroke Unit at the Nottingham University Hospitals National Health Service (NHS) Trust within 72 h after stroke. Participants will be randomised to receive usual care or usual care and early ES to the wrist flexors and extensors for 30 min twice a day, 5 days a week for 3 months. The initial treatment(s) will be delivered by an occupational therapist or physiotherapist who will then train the patient and/or their nominated carer to self-manage subsequent treatments.

**Ethics and dissemination:**

This study has been granted ethical approval by the National Research Ethics Service, East Midlands Nottingham1 Research Ethics Committee (ref: 15/EM/0006). To our knowledge, this is the first study of its kind of the early application (within 72 h post-stroke) of ES to both the wrist extensors and wrist flexors of stroke survivors with upper limb impairment. The results will inform the design of a definitive randomised controlled trial. Dissemination will include 2 peer-reviewed journal publications and presentations at national conferences.

**Trial registration number:**

ISRCTN1648908; Pre-results. Clinicaltrials.gov ID: NCT02324634.

Strengths and limitations of this studyThis is the first study to target reciprocally the flexors and extensors, which although should have therapeutic benefits with no contraindications noted, has been ignored by previous electrical stimulation research and clinical practice.Explores the feasibility of recruiting patients and starting interventional treatment very early after stroke (within 72 h).Incorporates mixed methods and a feasibility economic component.Includes short-term and long-term follow-up (3, 6 and 12 months postrandomisation).The assessor is not blinded in this small-scale feasibility study, but methods for ensuring assessor blinding in the subsequent definitive trial will be explored.

## Introduction

Every year in England approximately 110 000 people have a stroke, making it the largest cause of adult disability.^1^ Hemiparesis is the single most disabling factor after stroke, affecting around 80% of patients.^2^ Approximately 70% of patients with stroke experience impaired arm function, which is persistent and disabling for an estimated 40%.^2^ Loss of function reduces independence in activities of daily living (ADL)^3^ and impacts on an individual's quality of life. Stroke survivors who do not recover functional movement in the paretic arm are more likely to have pain than those who recover arm function,^4^ and are at risk of muscle atrophy and contractures, which can become established as early as 6 weeks following stroke.^5^ There is some evidence that 60% of stroke survivors have contractures^6^ and they are most common in the upper limb.^7^

Recent audit data demonstrate that patients with stroke are unlikely to receive the recommended 45 min^8^ per day of each therapy required, for a minimum of 5 days per week.^3^ In the very acute stages of stroke rehabilitation, to enable discharge emphasis is often placed on regaining trunk control and mobility at the expense of upper limb rehabilitation. Average time spent in upper limb activities ranges from 0.9 to 7.9 min per therapy session.^9^

Several upper limb treatments are used in clinical practice, with varying success. Some treatments such as constraint-induced movement therapy and mirror box therapy have evidence of benefit^10–12^ but success is confined to patients with some active movement in the wrist and hand, and many patients do not. There is evidence to support early initiation of therapeutic interventions after stroke, and strong evidence that intensity of treatment is an important factor in recovery.^13–15^

Electrical stimulation (ES) therapy has potential value for those with reduced or no arm movement after stroke. ES delivers a small, harmless current that depolarises a nerve leading to two actions: a contraction of a muscle via a motor nerve; and a sensory signal to the brain and spinal cord by stimulation of the associated sensory nerves. Stimulation of the muscle causes a contraction similar to a naturally produced contraction which could prevent muscle atrophy. The sensory stimulation of the brain and spinal cord can contribute to neuroplasticity^16^ and reduction of pain.^4^
^15^

Neuromuscular ES is a safe and harmless treatment for use in patient groups without the contraindications of uncontrolled epilepsy, pregnancy and those fitted with cardiac pacemakers. Metallic implants, cancerous lesions and risk of brittle bones around the stimulation site or the joint being treated are also contraindications. National clinical guidelines^2^ recommend routine use of ES for treating ‘foot drop’,^3^ but there is insufficient evidence to support the routine use in upper limb rehabilitation.^2^ Recently, Rosewilliam *et al*^17^ recruited 90 patients with no upper limb function 6 weeks after stroke and concluded that those who received ES of wrist extensors showed improved wrist extension, strength and grip. Secondary analysis concluded ES prevented the development of pain and deterioration in contractures.^4^

The ESCAPS study evaluates the feasibility of conducting a multicentre randomised controlled trial (RCT) of the efficacy and cost-effectiveness of early, intensive ES to prevent wrist joint deformities/contractures, weakness and upper limb pain after stroke. Qualitative components will explore barriers and facilitators to protocol adherence and clinical practice implementation.

The national clinical guidelines for stroke recommend that occupational therapists should aim to ‘re-educate’ the arm of patients who have reduced arm movement following stroke, by providing repetitive task training. This is inappropriate for many patients with stroke who do not have upper limb mobility. Treatment with ES does not require active movement; therefore, it could benefit patients who have severe to moderate arm function deficits.

This RCT is the first to study ES of flexors and extensors. Reciprocal stimulation of flexors and extensors will simulate the natural stretching movement and can be more effective in the prevention of contractures than stimulation of extensors alone. Flexor stimulation has been shown to reduce spasticity rather than being a contraindication.^18^
^19^

In order to prevent deconditioning of the forearm muscles, there is a need to initiate treatment within 72 h of stroke. Premature discontinuation of therapy may reduce any therapeutic effect. No extended trials have been conducted, so it is important to establish compliance and attrition rates.

To ensure that the results from the definitive trial are generalisable, cost-effective and implementable, the research-related ES treatment will be delivered by National Health Service (NHS) therapists instead of specialist research therapists. The best strategy for self-management needs to be identified, so that treatment may continue at home after discharge.

This work will help form the basis for a definitive trial in health economics from a societal perspective. Loss of arm and hand function results in reduction of productivity, having a huge impact on individual patients and society.

The NHS needs to find effective new ways of managing the upper limb after stroke. This research is important because it addresses the needs of a significant proportion of patients with stroke. The ESCAPS feasibility study will inform the design of a definitive multicentre RCT to evaluate the efficacy and cost-effectiveness of early ES to the wrist flexors and extensors.

## Methods and analysis

### Study objectives

The primary objective of the study is to evaluate the feasibility of a RCT that will test the efficacy of delivering early, intensive ES to prevent poststroke complications (such as pain and contractures) to the paretic (weak) upper limb after stroke.

The objectives of this feasibility study therefore are to determine whether:
It is feasible to recruit within 72 h after stroke event, and to ascertain recruitment rates.Initiating ES therapy within 72 h after stroke event is appropriate.The ES regime proposed, that is, to start receiving ES on an acute stroke unit twice a day, 5 days a week and to continue with this schedule postdischarge for up to 3 months in total, is feasible, as measured by compliance, attrition and the qualitative work.Study the interaction between compliance and response to treatment in order to identify the optimum compliance.To determine preliminary health economic information surrounding the costs and benefits of the intervention.

We will also determine in this feasibility study what the most appropriate inclusion/exclusion criteria are; what the most sensitive and acceptable outcome measures are; the optimum method for single blinding and any barriers to compliance to the protocol from both the therapist and patient perspectives.

### Participants

The study is set in Nottingham, England. Participants will be patients recruited from the Stroke Unit of the Nottingham University Hospitals NHS Foundation Trust within 72 h of stroke event.

### Inclusion criteria

Inclusion:
Confirmed clinical diagnosis of stroke;First stroke event to affect their upper limb;Aged >18 years;Impaired arm movement and strength caused by stroke (determined by the National Institute for Health Stroke Scale^20^ (NIHSS) arm subscore).

### Exclusion criteria

Exclusion:
An existing chronic upper limb condition (eg, peripheral nerve injury);Cardiac pacemaker;Pregnancy;Epilepsy;Undiagnosed pain or skin conditions (not related to the stroke).

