Scientific title	Early electrical stimulation to the wrist extensors and wrist flexors to prevent the post-stroke complications of pain and contractures in the paretic arm—a feasibility study
Countries of recruitment	England, UK
Health condition(s) or problem(s) studied	Stroke: prevention of post-stroke complications (eg, pain and contractures) in the upper limb
Intervention(s)	ES applied to the wrist extensors and wrist flexors for 30 min, twice a day, 5 days a week, for 3 months The ES will be set to deliver a 450 μs pulse at a frequency of 40–60 Hz (as per patient convenience). The intensity of the current will be increased to produce an alternating contraction of the flexors and extensors using a flex-hold-extend-hold pattern. A single stimulation and hold cycle will last 20 s and this will be cyclically repeated for 30 min Control group will receive usual care only and will not receive any ES treatment
Key inclusion and exclusion criteria	Inclusion criteria: Confirmed clinical diagnosis of first disabling stroke event affecting the upper limb Aged >18 years Impaired arm movement and strength (NIHSS arm subscore >0) resulting in reduced function, caused specifically by the stroke Exclusion criteria: Previous history of stroke affecting their upper limb Peripheral nerve injury/existing orthopaedic condition affecting the upper limb; fixed contractures at the elbow, wrist or fingers; malignancy in the area of the ES electrode placement; or epilepsy Cardiac pacemaker or similar implanted device Pregnancy Undiagnosed pain or skin conditions (not related to the stroke)
Study type	Feasibility RCT (single centre) Interventional Allocation: randomised Masking: unblinded (for practical reasons during the feasibility trial but in any subsequent pilot and definitive trials the outcomes assessor will be blinded)
Date of first enrolment	June 2015
Target sample size	40
Recruitment status	Recruiting

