### Adverse events

The occurrence of an adverse event as a result of participation is not expected and no adverse event data will be collected. The ES device itself is not under investigation and these devices have already passed extensive safety testing and are considered safe for use by patients with a range of conditions including stroke. Such devices are currently used in some areas of clinical practice on an ad hoc basis. The manufacturer's advice will be followed with regard to excluding patients who have a contraindication (eg, implanted cardiac pacemaker, epilepsy, pregnancy, malignancy in the area of the electrode placement).

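### Neither printed exclusion list names metallic implants or brittle-bone risk near the stimulation site, which the Introduction calls contraindications, and the shorter list omits two items found in Table 1

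*Protocol article*

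**What the plan says.** The protocol article deals with contraindications in four places.

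- **Introduction.** It calls ES safe for patients "without the contraindications of uncontrolled epilepsy, pregnancy and those fitted with cardiac pacemakers", and adds: "Metallic implants, cancerous lesions and risk of brittle bones around the stimulation site or the joint being treated are also contraindications".
- **Exclusion criteria.** The list is: "An existing chronic upper limb condition (eg, peripheral nerve injury);Cardiac pacemaker;Pregnancy;Epilepsy;Undiagnosed pain or skin conditions (not related to the stroke".
- **Table 1, key inclusion and exclusion criteria.** This list is longer. It includes "existing orthopaedic condition affecting the upper limb", "fixed contractures at the elbow, wrist or fingers; malignancy in the area of the ES electrode placement; or epilepsy" and "Cardiac pacemaker or similar implanted device".
- **Adverse events.** The manufacturer's "advice will be followed with regard to excluding patients who have a contraindication". The examples given are pacemaker, epilepsy, pregnancy and local malignancy.

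Under Recruitment, clinical ward staff screen each patient against the eligibility criteria before the research officers take over. Under Outcome measures, the numbers and percentages eligible and excluded after screening are among the primary feasibility outcomes.

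**The concern.** The article's statement that ES is safe is limited to patients without the contraindications it lists, so it depends on those patients being screened out. The list that ward staff would naturally work from does not prompt for two of the contraindications, and the longer list in Table 1 does not either. The two lists also differ from each other.

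Two things are at stake:

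- **Patient safety.** Under Intervention treatment, stimulation runs for 30 min twice a day, 5 days a week for 3 months. No therapist needs to be present, and patients or carers manage it themselves after discharge where possible. The Adverse events section plans no collection of adverse event data. Screening at entry therefore carries much of the protection.
- **Feasibility counts.** The numbers eligible and excluded depend on which criteria are applied, and Study objectives makes the choice of criteria a question for this study. The counts are easiest to interpret against one fixed list.

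**Working it through.** The article gives no figure to reproduce. The check is an item-by-item comparison of the six contraindications in the Introduction with the three places that govern exclusion.

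| Contraindication (Introduction) | Exclusion criteria | Table 1 | Adverse events examples |
|---|---|---|---|
| Epilepsy (Introduction: uncontrolled only) | named, unqualified | named, unqualified | named, unqualified |
| Pregnancy | named | named | named |
| Cardiac pacemaker | named | named, with similar devices | named |
| Cancer near the site or joint | not named | named | named |
| Metallic implant near the site or joint | not named | not named | not named |
| Brittle-bone risk near the site or joint | not named | not named | not named |
| **Named** | **3 of 6** | **4 of 6** | **4 of 6** |

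The same four items make up the union of the three columns, so 6 − 4 = 2 contraindications are named in none of them.

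**Differences between the two lists**

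1. Malignancy at the electrode site is in Table 1 only.
2. A device similar to a pacemaker is in Table 1 only. In context this means pacemaker-like devices, so it does not supply the missing item on metalwork in the arm.
3. Fixed contractures and orthopaedic conditions are spelled out in Table 1 only, but both plausibly fall under the general chronic upper-limb item in the Exclusion criteria section. That general item is arguably wider than the Table 1 wording. I do not count these as clear differences.
4. Previous stroke affecting the arm is an exclusion in Table 1 and is already covered by the first-stroke inclusion criterion, so only its placement differs.

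**Could other text supply the missing prompt?**

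- The general upper-limb items may catch some arm metalwork or bone disease, but they do not say so. Brittle-bone risk is the less clearly covered of the two.
- The rule under Adverse events is operative, but it is not part of the eligibility criteria.
- The therapist's initial assessment (Intervention treatment) is described as locating motor points and placing electrodes; no contraindication check is mentioned. It follows randomisation and takes place only in the ES arm. Under Study withdrawal, participants who withdraw after randomisation are not replaced. A contraindication found at that stage would be found too late and in one arm only.

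**The case against.** The strongest objection is that the Adverse events section already sets a rule wide enough to close the gap. It speaks of "excluding patients who have a contraindication (eg, implanted cardiac pacemaker, epilepsy, pregnancy, malignancy in the area of the electrode placement", and the examples are marked as examples, so an item missing from them is not thereby outside the rule. If the manufacturer's advice lists metalwork and fragile bone, such patients are excluded. This stands in part. The rule does cover local malignancy and may cover the other items. The advice and the screening form are not shown, so this cannot be settled from the article.

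A second objection is condensation. A journal article shortens its criteria, and the Table 1 row claims only to give key items. That would answer a complaint about silence. Here the article itself states the contraindications and then prints two unequal lists, both of which leave out the same two.

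A third objection is that the contraindications in question are confined to the area of the stimulation site or treated joint, where metalwork would often count as an orthopaedic or chronic upper-limb condition. This also stands in part, as overlap, but it does not amount to a prompt.

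A reader might infer that contraindicated patients are being enrolled, or that staff work from two different lists and the screening outcomes are distorted. The documents support neither. There is one centre, nothing shows two lists in use there, and no figure says how many patients would be affected.

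**Conclusion.** The point holds as a gap in the screening prompt. Two of the six contraindications that the article states are named in neither exclusion list, and the Exclusion criteria section also lacks two items that Table 1 has. It is minor, and worth correcting because the correction is cheap and bears on patient safety.

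It changes no sample size, error rate or analysis. The effect on the counts of eligible and excluded patients is only potential: it would arise if the criteria applied at screening differed from those against which the counts are later read.

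The verdict assumes that ward staff screen from the printed eligibility criteria, as Recruitment implies. If the screening form already carries the manufacturer's full list, the safety part falls away and only inconsistent text remains.

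**What to change.** Use one exclusion list in the Exclusion criteria section, in Table 1 (and the registry entry it reproduces) and on the screening form. It should contain:

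- all the Table 1 items, with epilepsy left unqualified;
- the general item on chronic upper-limb conditions from the Exclusion criteria section;
- a new item for a metal implant, or a risk of brittle bone, close to the stimulation site or the treated joint.

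Count eligible and excluded patients, as planned under Outcome measures, against that list.

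The cost is a protocol amendment after recruitment began on 1 June 2015. Under Trial management and regulatory issues it needs agreement from the Trial Management Group, the steering consultant and the sponsor, then permission from the Research Ethics Committee and notification of the local R&D office. The screening form and registry entry would need updating, and a few more patients may be excluded. If the form already carries these items, the work is largely aligning the text.

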### Recruitment

For this feasibility study, we aim to recruit 40 participants over a period of 17 months from one centre (the Nottingham Stroke Unit at the Nottingham University Hospitals NHS Trust). The Clinical Research Network (CRN) stroke research officers will be notified by the clinical ward staff of newly admitted (within 72 h post-stroke) patients with stroke who meet the eligibility criteria. The clinical staff will have screened the patient against the eligibility criteria and those patients that meet the eligibility criteria will be informed of the study, and asked if they give voluntary consent. If the participant lacks capacity to consent for themselves, consent will be sought from an approved consultee according to the Mental Capacity Act. A stroke research officer will visit the patient on the ward to explain the study further and answer any questions.

### Study design

The ESCAPS study is a quantitative single-centre feasibility RCT (n=40) with an embedded qualitative component to evaluate patient recruitment within 72 h of stroke to receive either routine care with ES or routine care only.

The RCT is designed as a parallel group, two-arm superiority trial with 1:1 allocation ratio.

The embedded qualitative component will explore:
Practical implementation issues such as acceptability of ES treatment to patients and adherence to ES treatment protocol,Potential barriers and facilitators to incorporation of ES treatment into routine practice, such as training of therapy staff.

Using:
Three focus groups with physiotherapists (n=4) and occupational therapists (n=4) involved in delivering and supporting the ES intervention;Semistructured interviews with a purposive subsample representing a range of ages, gender and stroke severity of patient participants and their nominated carers (intervention group (n=10); control group (n=5)).

Preliminary economic analysis will test the feasibility of collecting economic data using a patient resource use questionnaire.

A schematic diagram of the schedule and time commitment for trial participants in each study group is included as figure 1.

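### The interviews meant to explore adherence are sampled on age, gender and stroke severity, so nothing ensures that they include enough people who stopped ES or used it little

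*Protocol article*

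**What the plan says.** Under Study design, the protocol article specifies "Semistructured interviews with a purposive subsample representing a range of ages, gender and stroke severity of patient participants and their nominated carers", 10 for the intervention group and 5 for the control group. Nowhere does the article make adherence, low use, stopping ES or withdrawal a basis for choosing interviewees.

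The same section gives the qualitative component the task of exploring "Practical implementation issues such as acceptability of ES treatment to patients and adherence to ES treatment protocol". The Introduction says much the same: "Qualitative components will explore barriers and facilitators to protocol adherence and clinical practice implementation". It also warns that "Premature discontinuation of therapy may reduce any therapeutic effect". Under Study objectives, the question is whether the ES regimen "is feasible, as measured by compliance, attrition and the qualitative work", so the qualitative work is one of three stated measures of feasibility.

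Other parts of the article bear on stopping:

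- **Outcome measures:** the tolerability outcome counts withdrawals and refusals and records why ES was declined.
- **Data analysis:** reasons for loss to follow-up are summarised.
- **Adherence to treatment:** use is captured by device memory and a diary.
- **Intervention treatment:** people who stop ES are kept in follow-up where possible.
- **Obtaining informed consent from participants:** people without capacity are not interviewed, but their carers may be.

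**The concern.** Purposive sampling picks cases for what they can tell about the question. The question here is adherence and acceptability, yet the named dimensions are two demographic ones and severity. A sample can meet that frame in full and still consist almost entirely of people who carried on with ES.

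Stopping is a realistic prospect. The regimen runs twice a day, 5 days a week, for 3 months, and much of it is self-managed or carer-managed after discharge. The protocol itself foresees discontinuation. People who gave ES up, or used it little, can describe at first hand what got in the way and what would have kept them going. If the interviews hold none or only one of them, the definitive trial has a thin basis for changing the regimen or the support around it.

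**Working it through.** The article gives no calculated figure on this point: the interview numbers are stated without derivation, so there is nothing to reproduce. The calculation below is an illustration of how often the stated frame could leave stoppers out.

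**Inputs**

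- Total sample: 40 (Recruitment: "we aim to recruit 40 participants over a period of 17 months from one centre").
- Allocation: 1:1 (Study design: "parallel group, two-arm superiority trial with 1:1 allocation ratio"), so the ES arm has about 40/2 = 20.
- ES-arm interviews: 10 (Study design), taken first as 10 ES patients.
- Number who stop, k: not given in the article. Values of 3, 4 and 6 are assumed, which is 15%, 20% and 30% of 20.

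**Step 1. Selection unrelated to stopping.** The number of stoppers interviewed is hypergeometric:

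- P(none) = C(20−k, 10) / C(20, 10)
- P(exactly one) = k × C(20−k, 9) / C(20, 10)
- C(20, 10) = 184,756

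| k | P(none) | P(exactly one) | P(at most one) | Expected number (10k/20) |
|---|---|---|---|---|
| 3 | 19,448/184,756 = 0.105 | 3 × 24,310/184,756 = 0.395 | 0.50 | 1.5 |
| 4 | 8,008/184,756 = 0.043 | 4 × 11,440/184,756 = 0.248 | 0.29 | 2.0 |
| 6 | 1,001/184,756 = 0.005 | 6 × 2,002/184,756 = 0.065 | 0.07 | 3.0 |

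**Step 2. Stoppers harder to reach (assumption).** Suppose that at each draw a stopper has half the weight of a continuer (Wallenius noncentral hypergeometric, odds 0.5). Then P(none) is the product over j = 0 to 9 of (20−k−j) / (20−k−j + 0.5k):

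- k = 3: (17/18.5) × (16/17.5) × … × (8/9.5) = 0.30
- k = 4: (16/18) × (15/17) × … × (7/9) = (8 × 7)/(18 × 17) = 0.18
- k = 6: (14/17) × (13/16) × … × (5/8) = (7 × 6 × 5)/(17 × 16 × 15) = 0.05

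Under the same assumption, P(at most one) is 0.78, 0.62 and 0.30. The article gives no basis for the weight of one half; it only shows the direction and rough size of the effect.

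**Step 3. If the 10 counts carers as well as patients.** The wording leaves this open. If only about 5 ES patients are interviewed (assumed), with no reach penalty, P(none) = C(20−k, 5) / C(20, 5), and C(20, 5) = 15,504:

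- k = 3: 6,188/15,504 = 0.40
- k = 4: 4,368/15,504 = 0.28
- k = 6: 2,002/15,504 = 0.13

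This step treats a carer's interview as no substitute for the patient's, which is pessimistic: a stopper's carer could supply part of the account.

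**Reading.** On a neutral draw of 10 patients, a complete miss is unlikely once four or more stop. Having one stopper or none remains quite possible when three or four stop. Both risks rise if stoppers are harder to interview or fewer patients are interviewed.

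**The case against.** The strongest reply is that the trial does not depend on these interviews to learn about stopping. Tolerability is a primary outcome, with reasons recorded when ES is declined. Reasons for loss to follow-up are summarised, and device memory and diaries show use. Therapist focus groups and carer interviews add further views. All of this stands. A reader might infer that reasons for stopping would be lost altogether, and the article does not support that: what may be missing is depth.

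A reader might also infer that favourable interviews would make the regimen look more feasible than it is. The article does not support that either. Compliance and attrition are counted across all ES participants and stand beside the qualitative work in the feasibility objective, so discontinuation would remain visible.

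Nor does the article show that the sample leans towards people who carried on. Stopping ES is distinct from leaving the trial. Those who stop are retained where possible, and researchers visit participants at 3, 6 and 12 months, so many stoppers should be reachable. The half-weight figures are an assumption.

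Two further replies carry less weight. A random draw is not purposive selection, and interviewers might seek out stoppers anyway. That is possible, and nothing excludes stoppers, but the stated frame does not ask for them. It is also said that the full protocol may hold more. Yet the article itself names the sampling dimensions and leaves out the one closest to the stated purpose. Figure 1 and the consent forms are not shown, so no claim is made about interview timing or consent wording.

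**Conclusion.** The point holds as a modest design improvement. The purposive frame does not match the job given to the interviews, and it leaves to chance or to the interviewers' initiative whether enough stoppers and low users are heard. Nothing in the article is contradictory here, and the randomised comparison is unaffected.

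The size depends on three unknowns: how many stop, whether they are as easy to interview as others, and whether the 10 counts patients only. Under the neutral assumptions the main risk is a thin account from one stopper or none; a complete miss is less likely. Confidence is good on what the frame says and moderate on how much it would matter in practice.

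**What to change.** In Study design, add ES-use status to the purposive frame for the intervention-group interviews, with three levels: continued, partial or low use, and stopped or declined. Within the same 10 interviews, reserve some places (for example 3, or all such people if there are fewer) for participants who stopped or used ES little, or for their carers. Tolerability records can identify those who stop or decline. Device memory and diaries, collected at the 3-month visit, can identify low users. It would also help to state whether the 10 and 5 count patients, carers or both.

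With a place reserved, stoppers cannot all be missed by design as long as at least one exists and they or their carer agrees to be interviewed. The change is a few words in the sampling frame and adds no interviews. The downside is slightly less spread on age, gender or severity among the 10.
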